## Abstract

**Introduction:**

The most frequent complications after abdominal surgery include a decrease or loss of appetite, abdominal distension, abdominal pain caused by reduced gastrointestinal motility, anal arrest with intestinal distension and defecation, and nausea and vomiting due to anesthetic and opioid analgesic administration. These complications severely affect postoperative recovery, prolong hospital stay, and increase the financial burden. The objective of this study is to investigate the efficacy and safety of three acupoint stimulation modalities (electroacupuncture [EA], transcutaneous electrical acupoint stimulation [TEAS], and transcutaneous acupoint electrical stimulation combined with EA [TEAS+EA]), and two EA instrument waveforms (continuous wave and dilatational wave) for rapid recovery after abdominal surgery.

**Methods and analysis:**

A total of 560 patients will be recruited and randomly allocated to receive one of the following seven interventions: continuous wave EA, continuous wave TEAS, continuous wave TEAS + EA, dilatational wave EA, dilatational wave TEAS, dilatational wave TEAS + EA, and a control. For this study, continuous waves at 2 Hz, and dilatational waves at 2/50 Hz would be selected. The points to be stimulated by EA are the bilateral Neiguan (PC6), Hegu (LI6), Zusanli (ST36), Shangjuxu (ST37), and Xiajuxu (ST39), and TEAS would stimulate the bilateral Liangmen (ST21) and Daheng (SP15). The control group will neither receive EA nor TEAS. All patients will undergo an enhanced recovery plan after surgery and be provided with standardized perioperative management. Treatment will start on the first postoperative day and be administered once daily in the morning until the patient regains spontaneous bowel movements and can tolerate oral intake of solid food. The primary outcome is a composite of time to first defecation and time to tolerance of a solid diet. Secondary outcomes include time to first exhaustion; time of first defecation; time of tolerance of a solid diet; time to the first ambulation; length of hospital stay from surgery to discharge; visual analog scale score for postoperative daily pain, nausea, and vomiting; incidence of postoperative complications; and treatment acceptability.

**Discussion:**

This study will compare the efficacy and safety of three acupoint stimulation methods and two EA instrument waveforms for rapid recovery after abdominal surgery.

**Trial Registration:**

Chinese Clinical Trial Registry (http://www.chictr.org.cn), ChiCTR2100043883.

## Introduction

Postoperative complications of abdominal surgery include gastrointestinal dysfunction, pain, nausea, and vomiting (1, 2). These complications adversely affect the patient's quality of life, prolong the length of hospital stay, increase hospitalization costs, and the risk of needing a second operation (3). Therefore, reducing postoperative complications and promoting rapid recovery after surgery have been widely studied (4).

An Increasing amount of clinical evidence supports the use of acupuncture for enhanced recovery after surgery (ERAS) (5–7). Nevertheless, there is no unified standard for the use of specific acupuncture methods, acupoint selection, and electroacupuncture (EA) instrument parameters (8, 9). The majority of previous studies evaluating the use of acupuncture during postoperative rehabilitation after abdominal surgery have utilized distal limb acupoints (10, 11). This may be related to the surgical wound after abdominal surgery and changes in the structure and state of the abdominal organs which affect the acupuncture procedure and its safety. However, emerging evidence in recent years has indicated that acupuncture applied to select abdominal or limb acupoints can lessen the degree of abdominal pain and distension (12, 13). The use of abdominal meridian points may be particularly effective in decreasing abdominal pain (14, 15). This study is based on many early clinical practices and on the application of EA at meridian points in the distal extremities where efficacy was compared with the addition of a safer transcutaneous electrical acupoint stimulation (TEAS) of the abdominal acupoints.

Stimulation parameters are critical factors for the effectiveness of EA, as different stimulation parameters will bring about different therapeutic effects (16, 17). The use of a continuous wave in EA results in muscle contraction, exciting sensation, and motor nerve. The continuous wave is the most commonly used waveform to strengthen the effect of acupuncture in the clinic. In contrast, dilatational waves can increase metabolism, promote blood circulation, and improve muscle weakness and other functions. Dilatational waves are frequently used to facilitate postoperative rehabilitation (18). To date, no studies have compared the effectiveness of these two waveforms in promoting rapid rehabilitation after abdominal surgery (19).

Therefore, the primary purpose of this randomized controlled study is to compare the efficacy and safety of three acupoint stimulation methods and two EA instrument waveforms in facilitating rapid recovery after abdominal surgery, with the overarching aim of informing the development of an objective and unified standard for acupuncture use to facilitate rapid postoperative recovery.

## Methods and analysis

### Study design

This is a prospective, single-center, parallel, single-blind, randomized controlled trial. Effectiveness and safety will be compared among three acupoint stimulation methods (EA, TEAS, TEAS+EA) and two EA instrument waveforms (continuous waves, dilatational waves) to determine their suitability for promoting them in postoperative rehabilitation. This study will be conducted in accordance with the principles of the Declaration of Helsinki. The “Standard Protocol Items: Recommendations for Interventional Trials” checklist is provided in Supplementary Material 1.

### Recruitment

This trial will be conducted from 1 April 2021 to 31 March 2023, at West China Hospital of Sichuan University. A total of 560 patients who have undergone abdominal surgery (i.e., hepatobiliary, gastrointestinal, renal, or bladder tumor resection) and meet the study inclusion and exclusion criteria will be enrolled in this study. All patients will be requested to provide written informed consent prior to study participation. Figure 1 presents the study flow chart.

**Figure 1 F1:**
[figure not shown]
Flowchart of the study protocol.

### Inclusion criteria

Patients will be included if they (1) are aged 18–70 years old, male or female; (2) have undergone resection of hepatobiliary, gastrointestinal, renal, or bladder tumors under general anesthesia; and (3) participate voluntarily and provide written informed consent.

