### Randomization and blinding

This study has a single-blind design. Patients will be unaware of their group allocation, which will only be known to the lead investigator and acupuncture physician. The randomization sequence and allocation ratio (1:1:1:1:1:1) will be generated using the statistical software SPSS 26.0. Group allocation will be concealed using opaque envelopes, which will be distributed sequentially after patient enrolment.

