### Outcome measures

#### Primary outcome

The primary outcome is Gastrointestinal-2, which is a composite outcome of time to first defecation and time to tolerance of a solid diet (22).

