### Sample size

The determination of the sample size was based on the following pre-experimental results for the primary outcome measure, Gastrointestinal-2: cEA, 84.8 ± 36.1 h; cTEAS, 86.8 ± 40.1 h; cTEAS+EA, 70.3 ± 39.3 h; dEA, 78.3 ± 42.2 h; dTEAS, 81.2 ± 44.2 h; dTEAS+EA, 64.1 ± 36.3 h; and control, 110.8 ± 42.3 h. PASS 15 software was used to determine the sample size of 560 patients (80 patients in each group; α = 0.05 [two-sided], β = 0.1 [90% power], with an assumed 20% dropout rate).

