### Statistical analysis

The data will be analyzed using SPSS 26.0. All statistical tests will be two-sided, and a *p*-value of less than 0.05 will be considered statistically significant. Measurement data conforming to a normal distribution will be expressed as mean ± standard deviation (x ± s). Comparisons among groups will be performed *via* one-way analysis of variance, using the Student–Newman–Keuls q-test for pairwise comparisons. Variables that do not follow a normal distribution will be analyzed with the Kruskal–Wallis H-test. Categorical and count data will be described as frequency or percentage and compared among groups using the chi-square or Fisher's test.

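### Four kinds of tumour resection are pooled, but the stated GI-2 comparison ignores surgery type, which is known before allocation: an avoidable loss of precision

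*Protocol article*

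**What the plan says.** Under Inclusion criteria, the protocol article accepts patients who "have undergone resection of hepatobiliary, gastrointestinal, renal, or bladder tumors under general anesthesia". The Recruitment section repeats the same four groups. It gives neither a quota nor an expected share for each.

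The outcome is set under Primary outcome: "The primary outcome is Gastrointestinal-2, which is a composite outcome of time to first defecation and time to tolerance of a solid diet".

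Under Randomization and blinding, an SPSS-generated sequence is used and "Group allocation will be concealed using opaque envelopes, which will be distributed sequentially after patient enrolment". No stratification factor is named.

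Under Statistical analysis: "Comparisons among groups will be performed *via* one-way analysis of variance, using the Student–Newman–Keuls q-test for pairwise comparisons". The alternative is: "Variables that do not follow a normal distribution will be analyzed with the Kruskal–Wallis H-test". Neither method, as named, contains a covariate or a stratum.

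**The concern.** Patients enter after their operation and envelopes are handed out after enrolment, so the type of resection is on record before allocation in every case. For an outcome built on defecation and solid diet, whether the bowel itself was operated on is an obvious candidate predictor. A one-way comparison of arm means or ranks makes no use of it.

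Any variance in GI-2 that lies between surgery types is then counted as random error in all comparisons. It also lets arms differ by chance in their share of slow-recovery operations without any correction. The comparisons of modality and waveform are part of the stated purpose, and the pilot differences between waveforms are small beside the spread of the outcome. Those comparisons can least afford noise that could be removed.

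**Working it through.** **Inputs (Sample size section).** Pilot GI-2 in hours: "cEA, 84.8 ± 36.1 h; cTEAS, 86.8 ± 40.1 h; cTEAS+EA, 70.3 ± 39.3 h; dEA, 78.3 ± 42.2 h"; dTEAS 81.2 ± 44.2, dTEAS+EA 64.1 ± 36.3, control 110.8 ± 42.3. The plan has 80 per arm, or 80 × 0.8 = 64 evaluable after the assumed 20% dropout.

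**The plan's own figure.** The article does not name its formula. The smallest active-versus-control contrast comes close: cTEAS v control, 110.8 − 86.8 = 24.0 h, with SD √((40.1² + 42.3²)/2) = 41.2 h.
- Normal approximation: n = 2 × (1.960 + 1.282)² × 41.2² / 24.0² ≈ 62 per arm; 62/0.8 → 78 per arm, 546 in total.
- t-test: 63 per arm; 63/0.8 → 79 per arm, 553 in total.

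Both are within 3% of 80 and 560. The sample size thus fits a comparison with control and makes no use of surgery type.

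**Spread and standard error.** Pooled SD = √(mean of the seven squared SDs) = 40.2 h. SE of a two-arm difference = 40.2 × √(2/n) = 6.4 h at n = 80 and 7.1 h at n = 64.

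**Effect of adjusting.** Let R² be the share of within-arm GI-2 variance explained by surgery type. The document gives no value, so a range is assumed. The SE falls by the factor √(1 − R²), and the equivalent gain in patients is 1/(1 − R²) − 1. The chance case-mix shift between two given arms has SD √R² × SE.

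| Assumed R² | Cut in SE | Worth in patients | Residual SD | SD of chance shift, n = 80 / 64 | P(shift ≥ 6.2 h), n = 80 / 64 |
|---|---|---|---|---|---|
| 0.10 | 5% | +11% | 38.1 h | 2.0 / 2.2 h | 0.2% / 0.6% |
| 0.20 | 11% | +25% | 35.9 h | 2.8 / 3.2 h | 2.9% / 5.1% |
| 0.30 | 16% | +43% | 33.6 h | 3.5 / 3.9 h | 7.5% / 11.1% |

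Four surgery types cost three degrees of freedom. With 7 × 64 = 448 evaluable patients, the error degrees of freedom go from 441 to 438, which is negligible.

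**Set against the pilot waveform differences.** EA 84.8 − 78.3 = 6.5 h; TEAS 86.8 − 81.2 = 5.6 h; TEAS+EA 70.3 − 64.1 = 6.2 h; mean 6.1 h. For the 95% limit of the chance shift to reach 6.1 h, R² must be about 0.19 (n = 64) to 0.24 (n = 80). For its typical size (1 SD) to reach 6.1 h, R² must be 0.74 to 0.92.

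**What adjustment does for waveform power.** For one pair differing by 6.5 h with 64 per arm, power is about 15% unadjusted and 16%, 17% or 19% at R² = 0.10, 0.20 or 0.30. For the 6.1 h main effect (3 × 64 = 192 v 192), it is 32% unadjusted and 35%, 38% or 43% adjusted. Even at R² = 0.30, 90% power for a 6.5 h pair needs 562 per arm.

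**The case against.** Several points on the other side are sound.

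- **No figure by surgery type.** The document does not report GI-2 by type, the expected mix or an R². A marked difference in recovery is clinically plausible but not shown. This stands, and the size is therefore given only as a range.
- **The noise may already be budgeted.** If the pilot had the trial's case mix (not stated), its SDs of 36 to 44 h include the between-type variance. This stands too. The point is that the variance can be removed, not that it comes on top of the planned SD.
- **The randomised comparison is valid without adjustment.** Chance imbalance is covered by the type I error rate. Pooling several operations for breadth is a legitimate choice.
- **The comparisons with control are little threatened.** Their pilot differences run from 24.0 h to 110.8 − 64.1 = 46.7 h, against a shift SD of 2 to 4 h.

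A defence that leaves the matter to a fuller plan is weaker. The one-way analysis is stated outright, so a primary analysis adjusted for surgery type would replace it, not fill a gap.

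Three stronger readings are tempting and are not supported:

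- **That case-mix imbalance is as large as the waveform differences.** Suppose 25% of patients are in one type and that type differs by 36 h (both assumed). The expected largest gap in share over all seven arms is 13.1 to 14.6 points, or 4.7 to 5.3 h. For one given pair, the SD of the gap is √(2 × 0.25 × 0.75/n) = 6.8 to 7.7 points, or 2.5 to 2.8 h. The second figure is the one to set beside a single waveform pair. Only the total SE (6.4 to 7.1 h) is as large as the waveform differences.
- **That allocation is known to be unstratified.** The article is silent on this, and a condensed article may omit such detail.
- **That transurethral bladder resections are clearly let in.** The criterion does not exclude them in words, but the Recruitment section describes the population as having had abdominal surgery. At most this calls for clarification; whom to enrol is the sponsor's choice.

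**Conclusion.** The concern holds as a matter of efficiency. The stated primary comparison leaves out a baseline factor that is known before allocation, recorded for every patient and plausibly related to the outcome. If surgery type explains 10% to 30% of GI-2 variance, the precision forgone is worth 11% to 43% more patients. That range is an assumption; a smaller share would mean a smaller gain. Nothing here shows systematic bias or an inflated type I error. Nor should a reader infer that adjustment rescues the waveform question: its power stays low because of the sample size.

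**What to change.** Prespecify surgery type (hepatobiliary, gastrointestinal, renal, bladder) as a factor in the primary GI-2 analysis, before outcomes are examined by arm. A linear model with arm and surgery type would serve, with the pairwise comparisons taken from that model. If a rank test is kept for non-normal data, use a van Elteren-type test stratified by surgery type. Report the number of patients of each type in each arm.

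The planned recruitment period ended on 31 March 2023, so the analysis change is the part that can be made in any case. If allocation is still open and not already stratified, stratify it by surgery type as well. If it was stratified, say so and carry the factor into the analysis.

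The cost is one extra model term and a little more analysis work. Surgery type follows from the eligibility check, so no new data collection is needed.

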### Exclusion criteria

The exclusion criteria would comprise the following: (1) the surgical incision was made through the abdominal acupoints selected for this study; (2) local skin infection is evident at the selected acupoints; (3) patients are unable to understand or cooperate with the assessments (e.g., visual analog scale [VAS]); (4) metal allergy or severe fear of acupuncture, TEAS, or EA; (5) uncontrolled diabetes, severe coagulopathy, or cardiac, central nervous system, or psychiatric disorders; (6) pacemaker; and (7) concurrent enrolment in other research trials.

### Withdrawal criteria

Patients will be withdrawn from the study if they (1) experience serious adverse events, (2) have a serious complication or illness during the study that requires urgent action; or (3) withdraw informed consent.

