#### Secondary outcomes

Secondary outcomes comprise the following: (1) time of first spontaneous exhaustion after operation; (2) time of first spontaneous defecation after operation; (3) time of first tolerance to oral intake of solid food after operation; (4) time to first ambulation after surgery; (5) VAS scores for postoperative daily pain and nausea and vomiting; (6) postoperative daily incidence of nausea and vomiting; (7) length of hospital stay, from surgery to discharge; (8) incidence of postoperative complications; and (9) acceptability of acupuncture therapy on a 5-point Likert scale (very acceptable, moderately acceptable, somewhat acceptable, moderately unacceptable, and totally unacceptable).

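### Patients with serious adverse events or complications are withdrawn from the study rather than only from stimulation, so outcome-related losses can bias the Gastrointestinal-2 and length-of-stay comparisons in either direction

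*Protocol article*

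**What the plan says.** All references are to the protocol article.

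- **Withdrawal criteria.** The section opens "Patients will be withdrawn from the study if they (1) experience serious adverse events". Its second ground applies to patients who "have a serious complication or illness during the study that requires urgent action". Withdrawal of consent is a separate third ground, so the first two also remove patients who would be willing to stay under observation. The object of withdrawal is the study, not the stimulation.
- **Primary outcome.** GI-2 is "a composite outcome of time to first defecation and time to tolerance of a solid diet", planned in hours.
- **Secondary outcomes.** These include "incidence of postoperative complications", length of stay from surgery to discharge, and four further recovery times (first exhaustion, defecation, solid diet, ambulation).
- **Statistical analysis.** Groups are compared by "one-way analysis of variance, using the Student–Newman–Keuls q-test for pairwise comparisons". Otherwise, "Variables that do not follow a normal distribution will be analyzed with the Kruskal–Wallis H-test".
- **Sample size.** 560 patients, 80 in each of seven groups, "with an assumed 20% dropout rate".

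**The concern.** The events that end participation are either outcomes themselves or likely to affect the outcomes. A serious complication after abdominal tumour resection belongs in the complication outcome, plausibly lengthens the stay, and plausibly delays bowel function and solid diet. Taking these patients out of the study stops observation of the people who say most about recovery and safety.

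The removal happens after randomisation, so the groups compared may no longer be those that were randomised. If stimulation changes the rate or kind of serious events, or if the threshold for calling an event serious differs by arm, the loss differs by arm. The article says that the lead investigator and the acupuncture physician know the allocation, and that the acupuncture physician records adverse events. It does not say who decides on withdrawal.

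At stake are the GI-2 and length-of-stay comparisons and the completeness of the complication comparison. A later analysis plan can choose how to handle missing values, but it cannot restore times that were never collected.

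**Working it through.** **Step 1. Follow one patient through the stated rules.** A patient has a serious complication before first defecation or before tolerating solid food.

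| Outcome | What the rules give |
|---|---|
| GI-2 | Not yet reached at withdrawal. ANOVA needs a number and Kruskal–Wallis a rank; without an imputed or assigned value the patient contributes neither |
| Length of stay | Discharge falls after withdrawal, so it is not observed |
| Complications | Later ones are not observed; whether the triggering one counts is undefined |

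A patient who reached GI-2 before the event keeps an observed time. The problem for GI-2 is confined to those withdrawn earlier.

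**Step 2. The plan's own sample size.** The smallest planned active-versus-control difference is continuous-wave TEAS: 110.8 − 86.8 = 24.0 h. Pooled SD = √((40.1² + 42.3²)/2) = 41.2 h. By the normal approximation, two-sided α = 0.05 and 90% power:

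n = 2 × (1.960 + 1.282)² × 41.2² / 24.0² ≈ 62 per group

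62 / 0.8 = 77.5, so 78 per group and 7 × 78 = 546 in total, close to the stated 80 and 560. The article does not name the procedure used in the software, so this is a plausible route and not a confirmed one.

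With 20% dropout, 80 × 0.8 = 64 per group remain and power for this contrast is about 91%. With all 80 analysed it is about 96%. The allowance therefore does its job for power. It has no effect on bias from losses that depend on outcome.

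**Step 3. Illustrate the possible bias.** Planning figures: continuous-wave electroacupuncture (cEA) 84.8 ± 36.1 h, control 110.8 ± 42.3 h, difference 110.8 − 84.8 = 26.0 h. Assumed, because the documents give no rate: 5% or 10% of an arm is lost, and those lost are its slowest patients. For a given loss, that is the most an arm's mean can fall under the assumed distribution.

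Fall in the mean when the slowest fraction p is lost, with z the upper-p normal quantile:
- Normal times: SD × φ(z)/(1 − p). The multiplier is 0.1086 at 5% and 0.1950 at 10%.
- Lognormal times: mean × [1 − Φ(z − s)/(1 − p)], where s² = ln(1 + (SD/mean)²). This gives s = 0.408 for cEA and 0.369 for control.

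| Fall in mean (h) | Normal | Lognormal |
|---|---|---|
| cEA, 5% lost | 3.92 | 5.19 |
| cEA, 10% lost | 7.04 | 8.59 |
| Control, 5% lost | 4.59 | 5.95 |
| Control, 10% lost | 8.25 | 9.94 |

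Observed difference = 26.0 − (control fall) + (cEA fall):

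| Loss, cEA / control | Normal | Lognormal |
|---|---|---|
| 5% / 5% | 26.0 − 4.59 + 3.92 = 25.33 | 26.0 − 5.95 + 5.19 = 25.24 |
| 5% / 10% | 26.0 − 8.25 + 3.92 = 21.67 | 26.0 − 9.94 + 5.19 = 21.25 |
| 10% / 5% | 26.0 − 4.59 + 7.04 = 28.45 | 26.0 − 5.95 + 8.59 = 28.64 |

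The ceiling applies to each arm's mean, not to the difference, because the two falls partly cancel. If control lost its slowest 10% and the losses in cEA were unrelated to recovery, the difference would be 26.0 − 9.94 = 16.06 h to 26.0 − 8.25 = 17.75 h.

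**Step 4. False positives.** Two arms with the same lognormal distribution (mean 84.8, SD 36.1), 80 each, were simulated and compared by t-test at 5%. The rejection rate was 4.8% with no loss, 8.3% when each arm lost its slowest 5%, and 15.9% with 5% against 10%. The unequal loss accounts for only part of the last figure, since equal loss already raises the rate.

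**The case against.** The strongest reply is that the article never says that withdrawn patients are left out of the analysis. It is a condensed account, and analysis sets and missing-data handling commonly sit in a full protocol or analysis plan that is not shown. That silence is not a fault, and this point does not rest on it. It rests on the stated rule that ends participation in the study and on its effect on data collection.

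Several stronger readings are tempting, and the documents do not support them.

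- **That the complication outcome loses its own events.** A complication must be recognised before it can trigger withdrawal, and nothing prevents it from being counted. What goes unobserved is what follows it; the status of the triggering event is undefined.
- **That the slowest recoveries are known to leave the primary analysis.** This is a reasonable inference, but the article gives no timing, rate or delay for such patients.
- **That 112 patients (0.20 × 560) are at issue.** That is total dropout for every reason, and no share is attributed to serious events.
- **That equal complication rates would remove the bias.** The delays would have to match too. Equal 5% losses of the slowest still move 26.0 h to about 25 h.
- **That the outcome must be analysed by Cox regression with censoring at withdrawal.** Censoring triggered by a complication would be informative and would leave the same bias. Once follow-up continues, most times are observed and the planned rank test can serve.

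It is also fair to say that the effect may be small if serious events are rare or mostly follow GI-2. That stands, and limits what can be claimed about size.

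**Conclusion.** The point holds as a conflict between the withdrawal criteria and the outcomes and tests that the article fixes. Followed as written, the rule creates a loss that arises after randomisation, is related to outcome and may differ by arm. It can bias GI-2 and length of stay in either direction and leaves the complication count incomplete or ambiguous.

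The size is unknown. Under the assumed 5% and 10% losses, with the slowest patients lost in both arms, the 26.0 h cEA–control difference falls by about 4.3 to 4.8 h or rises by about 2.5 h, depending on which arm loses more. These figures show scale and direction; they do not forecast the result. They rest on the planning means and SDs, normal or lognormal times, and loss rates that the documents do not supply.

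A reader might go further and infer that the plan deliberately restricts the analysis to uncomplicated completers, or that a spurious benefit is to be expected. Neither follows: exclusion is not stated, and the direction of any bias is open.

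**What to change.** Reconcile the withdrawal criteria with the primary outcome, secondary outcomes and statistical analysis sections:

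1. Distinguish discontinuing study treatment from withdrawing from follow-up. The clinical rule for when treatment stops is not in question here and stays as it is.
2. Continue to record GI-2, complications and length of stay to discharge for every patient who has not withdrawn consent.
3. Analyse all randomised patients in the group to which they were allocated.
4. State that the event that triggers discontinuation counts in the complication outcome.
5. For the few who never reach GI-2, use a rank analysis with 'not reached' placed last. The Kruskal–Wallis test already in the plan can do this.

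The cost is mainly wording, plus slightly more data collection. The extra data should lie in routine inpatient records; that is an assumption, since the article does not describe its data sources. Rank-based results or medians would be reported beside the means. The 560 patients need not change, as keeping these patients in follow-up can only help power through numbers.
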